## Abstract

**Background:**

Early childhood caries is a highly prevalent disease affecting young children. Parental brushing of children’s teeth is recommended during preschool years. Interventions to promote parental brushing of children’s teeth are assessed as a package in randomized clinical trials and the efficacy of separate components is not known.

**Methods and analysis:**

The aim of this study is to develop an optimized behavior modification intervention to increase parents’ brushing of their pre-school children’s teeth using the multi-phase optimization strategy (MOST) guided by the Theory of Planned Behavior. Behavior change will be assessed by the percent reduction in children’s dental plaque index after 6 months and parents reporting of toothbrushing frequency. Two phases of MOST will be carried out. First, the preparation phase comprises the development of a conceptual framework, identifying candidate components, conducting a feasibility pilot study to assess the acceptability and the design features of three intervention components (motivational interviewing (MI), and two mobile health (mHealth) components: oral health promotion messages and storytelling videos delivered using WhatsApp messenger) in addition to setting an optimization objective. Second, the optimization phase constitutes a factorial trial assessing the three intervention components and developing the intervention by selecting the most effective components within the optimization constraint. Each component will be set at two levels: yes (the intervention is applied) and no (the intervention is not applied). A linear regression model will be used to assess the effect of the intervention components on the percent reduction in dental plaque index (primary outcome measure). The secondary outcome measure is the change in the frequency of parents’ brushing of the child’s teeth. The combination of components making up the new optimized intervention will be selected.

**Discussion:**

This will be the first study to apply the MOST framework in the field of dentistry. The results of this study can guide the development of an optimized behavior modification interventions using mHealth and MI.

**Trial registration:**

ClinicalTrials.gov, NCT04923581, Registered 11 June 2021.

**Supplementary Information:**

The online version contains supplementary material available at 10.1186/s13063-021-05931-0.

## Background

Early childhood caries (ECC) is the most prevalent chronic disease affecting children worldwide with high prevalence in Egypt exceeding 50% [1, 2]. ECC has adverse effects on the growth and development of children and their quality of life as well as that of their caregivers [3]. Regular toothbrushing with fluoridated toothpaste is a highly effective home care measure [4], which renders dental health education of caregivers one of the best approaches to control this disease [5].

Parents are responsible for brushing their children’s teeth at young age to prevent dental caries [6, 7]. The American Academy of Pediatric Dentistry recommends parental supervision of children’s toothbrushing during preschool years [8]. Barriers to parents’ brushing of their children’s teeth include inadequately supportive and organized home environment, absence of flexibility in daily activities, and parenting styles lacking positive reinforcement and involvement [9, 10]. In addition, the child’s development, level of co-operation, and the surrounding community-level factors may influence toothbrushing [10].

Several theories were proposed to explain health behaviors and how they are affected by various factors and barriers. These theories include the social cognitive theory, the theory of diffusion of innovation, the theory of planned behavior (TPB) [11], and the health belief model [12]. The TBP was used to decipher barriers to behavior change in oral health education programs [13], to design behavior change interventions [14], to improve interventions by assessing participants’ background [15], and to promote parental brushing of children’s teeth [16]. The TPB can guide the development of interventions to promote parents’ brushing of their children’s teeth by addressing the impact of barriers affecting parents’ perceived control, their attitude toward oral health, and the norms they perceive regarding the value of oral hygiene.

Several interventions were developed [17] to promote parents’ brushing of children’s teeth and were assessed using randomized clinical trials (RCTs). These interventions usually consist of multiple components to maximize the efficacy of the intervention and are evaluated as a single package [18]. The multi-phase optimization strategy (MOST) assesses the effectiveness of each component in the intervention separately. MOST is an engineering-inspired framework that focuses on developing and optimizing an intervention according to a specific optimization objective so that components of the interventions can later be evaluated for effectiveness as a package in an RCT [18]. The aim is not only to develop an effective intervention but an efficient one too. Understanding the mechanisms by which an intervention produces its effects makes it possible to build upon previous interventions in a more systematic and gradual means [18]. MOST consists of three phases: preparation, optimization, and evaluation phases. The preparation phase lays the groundwork for the development of the conceptual framework and the identification of candidate intervention components using a feasibility pilot study. In the optimization phase, the optimized intervention is constructed using optimization trials. Finally, the effectiveness of the optimized intervention can be confirmed in the evaluation phase through an RCT.

We aim to use the MOST framework to engineer a behavior modification intervention to promote parents’ brushing of their pre-school children’s teeth using fluoridated toothpaste and to select intervention components and component levels with the greatest efficacy within a predefined optimization objective. We will select intervention components based on the constructs of the TPB then test them for acceptability in a feasibility pilot study representing the preparation phase of MOST. This will be followed by an optimization factorial design trial to compare the selected components and select the components with the greatest efficacy within predefined optimization objectives.

## Methods/design

### Overview of the study

I-The preparation phase, including:Developing a conceptual framework to guide the design of the interventionIdentifying candidate intervention componentsConducting a feasibility pilot study to determine the acceptability of the intervention components and identify the preferred frequency and timing of providing themSetting an optimization objectiveII-The optimization phase, including:Assessing the individual components using a factorial trial.Identifying the intervention components with greatest efficacy with the specified optimization objective.

#### I. Preparation phase

##### a. Conceptual framework

The TPB posits that intentions are predictors of behaviors and are affected by attitudes, subjective norms, and perceived control [19]. Individuals adopt beliefs about the outcomes of a behavior, and these beliefs contribute to their attitude. Subjective norms are the perception about the expectations of important others, and these contribute to the perception of social pressure and motivation to comply. Perceived control is divided into two components: self-efficacy which is the sense of ease/ difficulty in engaging in the behavior and controllability which is the extent to which the performance is up to the person. Parental attitude, self-efficacy, and intention are modifiable social-cognitive constructs that were reported to be significantly associated with preschool children’s oral hygiene behavior and can be targeted by behavior modification interventions [20]. In the proposed study, each TPB construct will be targeted by a component, and this is assumed to lead to the desired behavior modification (Fig. 1).

**Fig. 1 Fig1:**
[figure not shown]
Conceptual framework based on the TPB

##### b. Identifying candidate components (Table 1)

Three components are proposed in addition to a core/constant component provided to all participants. The three components are motivational interviewing (MI), oral health promotion messages (OHPM), and storytelling (ST). In a previous study, MI outperformed traditional oral health education in improving patient behaviors and oral health perceptions and enhancing clinical indicators (e.g., plaque index, gingival index, bleeding on probing) [21]. Another study [22] reported that messages based on subjective norms were the most effective in inducing behavioral changes. The use of story-based approaches also showed promising results in improving children’s oral hygiene [23].

**Table 1 Tab1:** Candidate intervention components

Intervention component	Target construct	Frequency of delivering the component	Method of delivery and setting
**Constant component**	Core knowledge	Once at baseline	Pamphlets in clinic
**MI**	Perception of control	1 MI session + 3 phone calls	Face to face in clinic + phone calls
**OHPM**	Perceived norms	Determined during the feasibility pilot study	mHealth: electronic messages via WhatsApp messenger
**ST videos**	Attitude	Determined during the feasibility pilot study	mHealth: electronic messages via WhatsApp messenger

*Constant component*: All participants will receive pamphlets emphasizing the importance of primary teeth, correct feeding habits, recommended sugar intake, and age-appropriate oral hygiene practices. Toothpaste samples will be distributed as tokens of appreciation. This component aims to provide standard basic oral health education and foster engagement and trust.

*Motivational interviewing*: A single 30–45-min MI session will be offered by one researcher (MI) experienced in motivational interviewing for promoting oral health care. This component will target the perceived control construct of the TPB. The researcher providing the MI will receive training using the MI network of trainers’ resources [24]. The MI session includes establishing rapport and encouraging participants to talk about their dental habits and what they want for their children to motivate them to accept changes in behaviors. Options and strategies for improving dental health will be discussed. After the session, parents will be contacted by phone every 2 months, for 6 months, to reinforce commitment to the new behavior and provide support. Without follow-up, new behaviors may not be maintained or even tried leading to relapse.

*Oral health promotion messages*: Teledentistry and mobile health (mHealth) are proving to be an effective tool for the promotion of oral health in various age groups [25]. mHealth components will be incorporated in the proposed study to reduce the time needed for parents to receive health education, adhere to physical distancing in the time of COVID-19, and make use of the popularity of these tools among the younger generations. A series of unique messages targeting the subjective norms construct of the TBP will be developed by the researchers (MI, MET, and WE) and sent to the parents using the WhatsApp Messenger [26]. The messages are based on previous studies [23, 27] and are modified to fit the proposed study. The validity, acceptability, preferred frequency, and timing of messages will be determined in the feasibility pilot study of the preparation phase (Appendix 1). Based on the frequency, the number of messages will be determined so that they are spread over the study period.

The following are examples of the messages:

“{name}, this is {dentist} from {clinic}. Did you know that brushing your children’s teeth twice daily using a toothbrush and toothpaste will help them have a nicer smile in front of their friends and family?”

“{name}, this is {dentist} from {clinic}. Ensure smaller dental bills for your family by brushing your child’s teeth twice daily using a toothbrush and toothpaste.”

“{name}, this is {dentist} from {clinic}. Be a role model for your children and show them how to brush their teeth twice daily using a toothbrush and toothpaste”.

*Storytelling videos*: Via WhatsApp messenger, the parents will receive another mHealth component: a series of 1-min videos targeting the attitude construct of the TPB and prepared by the investigators (MI, MET, and WE). The videos have a scenario narrating the experiences of parents whose children suffered from ECC, emphasizing the positive effect of tooth brushing and fluoridated toothpaste in controlling ECC, and enhancing children’s oral hygiene. The preferred frequency and timing of the videos will also be assessed during the preparation phase (Appendix 1) and based on the frequency; the number of videos will be determined.

##### c. Feasibility pilot study

The feasibility pilot study assesses the acceptability and features of MI, OHPM, and ST videos. The feasibility study is not planned to be powered. Ten to 16 parents will be recruited from the clinic of the Department of Pediatric Dentistry and Dental Public Health, Faculty of Dentistry, Alexandria University, Alexandria, Egypt, until information saturation occurs [28]. Each parent will receive and provide feedback on the MI session and phone calls, the OHPM, and the ST videos.

*Inclusion criteria for parents in the feasibility pilot study:*
a-Has children between 2 and < 5 years of ageb-Has children with dental plaque index scores ≥ 2 or visible plaque accumulation on maxillary anterior teethc-Literate and owns a mobile phone with WhatsApp messenger application or where WhatsApp messenger can be installedd-Willing to participate in the study

*Exclusion criteria:*
a-Parents of children with a definitely negative behavior (Frankel’s scale rating 4) [29]b-Parents of physically disabled or medically compromised childrenc-Parents of children who need emergency dental treatment

The parent will sign an informed consent form and receive the 3 components. The acceptability of the 3 components will be evaluated in a semi-structured interview using the framework of acceptability [30] assessing: affective attitude, burden, perceived effectiveness, ethicality, intervention coherence, and opportunity costs (Appendix 1). They will also be asked about the preferred frequency and timing of the messages and videos.

##### d. Setting the optimization objective

The optimization objective is to develop an intervention that fits within the time a parent is willing to spend receiving health education to support him/her to brush their child’s teeth. This objective may be more relevant in the mother and child health centers where the optimized intervention is planned to be provided. In this setting, parents receive ante- and post-natal care including health education. These services are provided free of charge by salaried providers, and thus, financial constraints and provider time may not be appropriate constraining factors. The key constraint [19] in the present study is the time the parent is willing to spend receiving the components. This time should cover commuting to and from the clinic to receive MI, the time of the phone call reminders for MI, the time to read the WhatsApp messages, and that spent watching the videos. It will be assessed using a questionnaire to the parents in the feasibility pilot study (Appendix 1).

#### II. Optimization phase

##### a. Factorial trial design

A factorial trial will be used to compare the levels of the three intervention components: MI, OHPM, and ST videos with the features identified during the preparation phase. Factorial designs are preferred for comparing the three components for two reasons. Firstly, factorial experiments separate component effects, enabling the estimation of the main effect and interactions between components. Secondly, factorial trials are efficient compared to alternative designs because they require fewer participants to achieve the same statistical power. Conducting three individual trials will require three times as many participants as the factorial trial.

*Study setting*: Outpatient clinics of the Department of Pediatric Dentistry and Dental Public Health, Faculty of Dentistry, Alexandria University, Alexandria, Egypt. This outpatient clinic is part of the largest public hospital in the city and is affiliated with Alexandria University. It receives hundreds of patients daily and is a suitable setting for patient recruitment.

*Eligibility criteria*: The inclusion and exclusion criteria are the same as those of the feasibility pilot study.

*Intervention components*: Each of the three components (MI, OHPM, and ST) has two levels: yes (the intervention is applied) and no (the intervention is not applied) as shown in Table 2. Participants will be divided into subgroups, each receiving one of the eight experimental conditions.

**Table 2 Tab2:** Factorial trial design in the optimization phase with 8 experimental conditions

Experimental condition	MI	OHPM	ST
1	No	No	No
2	No	No	Yes
3	No	Yes	No
4	No	Yes	Yes
5	Yes	No	No
6	Yes	No	Yes
7	Yes	Yes	No
8	Yes	Yes	Yes

*Outcome measures*: The outcome assessment uses validated methods and assessment tools including a clinical examination and a questionnaire. Therefore, these tools and methods will not be further assessed in the pilot feasibility study.

1. Primary outcome: Reduction in the dental plaque index scores of children of participating parents after 3 and 6 months [31] will be measured using the modified plaque index (PlI) of Silness and Löe [32] by another researcher than the one providing the intervention (NA). The World Health Organization (WHO) community periodontal index of treatment needs (CPITN) probe and a disposable dental mirror will be used to assess plaque on 6 index teeth (upper right 2nd primary molar, upper primary right lateral incisor, upper left 1st primary molar, lower left 2nd primary molar, lower left primary lateral incisor, and lower right 1st primary molar) at baseline and after 3 and 6 months. The four surfaces of each tooth will be scored from 0 to 3 and the scores will be averaged per tooth. The scores of the six teeth will be averaged to obtain the mean PlI of the child. The outcome measure is the percent reduction in dental plaque scores calculated as: [(plaque score after 3 or 6 months − plaque score at baseline)/ plaque score at baseline] × 100. The primary outcome measure is reduction in plaque index scores after 6 months.

2. Secondary outcome: Parent-reported frequency of brushing the child’s teeth using fluoridated toothpaste will be assessed by the Arabic version of the WHO questionnaire [33] at baseline, after 3, and 6 months. The questionnaire assesses the frequency of toothbrushing on a 7-point scale ranging from never to twice or more a day. The outcome measure is the change in frequency from baseline to 3 or 6 months categorized as increased (changing from lower to higher frequency), remained the same (reporting the same frequency) and decreased (changing from higher to lower frequency). (Appendix 2)

3. Moderators such as child’s age and sex, the number of children in the family, parents’ age, oral hygiene practices, and education level will be assessed by the questionnaire.

*Participant timeline*: Participant timeline is shown in Fig. 2.

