**Fig. 2 Fig2:**
[figure not shown]
Flow chart of participants throughout the factorial trial of the optimization phase

*Sample size calculation*: The study is powered to detect at least a medium effect size measured by partial eta squared (*ƞ*^2^) = 0.06; the effect size measure for factorial ANOVA [34]. In G* Power 3.0.10 [35], we specified *f*= 0. 0.2526456 based on the required *ƞ*^2^, alpha error= 5% and study power= 80%. For the 8 conditions in Table 2, we used numerator df= (2 levels in MI- 1) X (2 levels in OHPM- 1) X (2 levels in ST videos- 1) = 1 X 1 X 1= 1. A total sample size of 126 will allow the estimation of main effects and interactions using linear regression analysis. This will be rounded to 160 corresponding to 20 parents in each of the 8 experimental conditions.

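### The secondary outcome reduces a 7-point brushing scale to direction of change, which weakens the trial's conclusion about brushing at no saving in data collection

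*Protocol article*

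**What the plan says.** In the protocol article, under Factorial trial design, item 2 of the outcome measures describes the instrument for the secondary outcome: "The questionnaire assesses the frequency of toothbrushing on a 7-point scale ranging from never to twice or more a day". It is completed at baseline, 3 and 6 months. The same item then fixes the outcome measure as the change from baseline, "categorized as increased (changing from lower to higher frequency), remained the same (reporting the same frequency) and decreased".

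The Sample size calculation concerns an effect expressed as partial eta squared in a factorial ANOVA and claims no power for brushing. The regression under Data management and statistical analysis is named for percent reduction in plaque only. Component selection is described through the size of a main effect, with an increase in plaque as the example of a wrong direction.

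**The concern.** Two consequences follow from the definition itself and need no assumption.

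- **Size of change is lost.** One step up from never and six steps up, from never to the top category, both count as increased. All three example messages under Identifying candidate components refer to brushing twice daily, yet the coded outcome cannot show how many parents got there.
- **The possible score depends on where the parent starts.** A parent at the top at baseline can only be scored as same or decreased. If that parent keeps brushing at least twice daily, the score equals that of a parent who never brushes throughout. Eligibility is based on plaque, and no criterion on brushing frequency keeps such parents out.

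Parental brushing is the behaviour the intervention targets, and this is the only outcome that measures it directly. A coarser outcome makes it harder to see a component's effect on that behaviour.

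**Working it through.** **1. The plan's own figure.** The inputs are in the Sample size calculation: partial eta squared 0.06, f given as "0.2526456 based on the required" effect size, and "alpha error= 5% and study power= 80"%.

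- f = √(0.06/0.94) = 0.2526, as stated.
- Noncentral F with 1 and N − 8 degrees of freedom, λ = f²N. At N = 126, λ = 0.06383 × 126 = 8.04 and power is 0.803. At N = 160, λ = 10.21 and power is 0.888.
- The stated 126 is reproduced. It belongs to the plaque outcome.
- The equivalent standardised difference between the yes and no levels is d = 2f = 0.505.

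**2. Simulation for the brushing outcome.** From the documents: 160 parents, hence 80 yes against 80 no for each component; seven categories; two-sided 5%. The remaining inputs are assumed, because the documents do not give them:

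- share at the top category at baseline: 5%, 15% or 30%;
- latent correlation ρ between baseline and 6 months: 0.3, 0.5 or 0.7;
- improvement common to all parents: 0.3 SD;
- component effect: 0.505 latent SD, or 0.505 residual SD, i.e. 0.505 × √(1 − ρ²), which is 0.437 at ρ = 0.5.

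That makes 3 × 3 × 2 = 18 scenarios, with 1,500 runs each (standard error of a power estimate at most about 1.3 points). A latent normal variable was cut into seven categories. The other two components were left out. Four analyses are compared:

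- A: three categories, unadjusted (Mann-Whitney);
- B: numeric change, unadjusted (t test);
- C: three-category score, linear model with baseline;
- D: 7-point score at 6 months, linear model with baseline.

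The table shows the middle case and the scenarios at the ends of the main ranges:

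| Top at baseline | ρ | Effect (SD) | A | B | C | D | D − C | D − A |
|---|---|---|---|---|---|---|---|---|
| 5% | 0.7 | 0.505 | 0.892 | 0.947 | 0.932 | 0.984 | 0.052 | 0.092 |
| 15% | 0.5 | 0.437 | 0.527 | 0.622 | 0.654 | 0.823 | 0.169 | 0.296 |
| 30% | 0.3 | 0.482 | 0.405 | 0.447 | 0.591 | 0.773 | 0.182 | 0.368 |
| 30% | 0.3 | 0.505 | 0.448 | 0.499 | 0.645 | 0.825 | 0.180 | 0.377 |
| 30% | 0.7 | 0.361 | 0.448 | 0.559 | 0.563 | 0.723 | 0.160 | 0.275 |

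**3. Reading the results over all 18 scenarios.**

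- Collapse alone, both analyses adjusted (D − C): 5 to 18 points.
- Collapse alone, neither adjusted (B − A): 4 to 12 points.
- Collapse and lack of adjustment together (D − A): 9 to 38 points. Power is 0.41 to 0.89 for A and 0.72 to 0.98 for D.
- In the middle case the 29.6-point gap splits into 16.9 points for the collapse (0.823 − 0.654) and 12.7 points for moving from A to C (0.654 − 0.527), which is mainly the baseline adjustment.

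The three-category outcome was the weaker one in every scenario. Analysis D is a linear model and stands in for the ordinal model proposed below; the ordinal model itself was not simulated here.

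**The case against.** The strongest reply is that the damage is small and partly not of the plan's making.

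- **The gap of up to 38 points.** A reader might blame all of it on the three categories. That is not supported: the comparison also sets an unadjusted analysis against an adjusted one. The article names no model for the brushing outcome, so the lack of adjustment is a silence of the kind a condensed article may leave to the full protocol or the analysis plan. Only the coding is fixed, and only the 5 to 18 points (4 to 12 without adjustment) belong to it.
- **Component selection.** A reader might infer that the coding could lead to a useful component being dropped. The selection procedure illustrates its rule with plaque, 6-month plaque is the primary outcome, and no section gives brushing a part in selection.
- **The sample size.** A reader might infer that it is too small. It is set for another outcome, it reproduces, and no power is claimed for brushing.
- **The ceiling.** It lies partly in the scale: a numeric change score would also give zero to parents already at the top. Plaque-based entry probably keeps their number low, so the 30% scenarios may be pessimistic.
- **Simplicity.** Direction of change is easy to read, and a 7-category model with 20 parents per condition may meet sparse categories.

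All of this stands as a limit on size and reach. It does not remove the loss of information, which the definition itself produces.

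**Conclusion.** The point holds in a limited form. As defined, the secondary outcome discards the size of change, cannot show attainment of twice-daily brushing, and scores sustained best behaviour the same as sustained absence of brushing. These follow from the definition alone.

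The power cost is certain only in direction. Under the assumed baseline distributions, correlations and effects, the collapse itself costs about 5 to 18 points for one component at N = 160 when both analyses adjust for baseline. The 9 to 38 points against a baseline-adjusted 7-point analysis apply only if the three-category outcome is analysed unadjusted, and part of that gap comes from the adjustment. The consequence is a weaker secondary conclusion about brushing. The primary analysis, the stated sample size and the selection rule as described are unaffected.

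**What to change.** Define the secondary outcome as the 7-point brushing frequency at 6 months, with 3 months as a supporting time point. Analyse it with an ordinal (proportional-odds) model containing the three effect-coded components, their interactions and baseline frequency, merging adjacent sparse categories if needed. Also report, by component level, the proportion of parents brushing at least twice daily. Keep the increased, same or decreased table as a descriptive display.

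Using the follow-up category with baseline as a covariate, rather than a numeric change score, avoids counting sustained top-category brushing as no improvement.

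The cost is wording: the 7-point data are already collected at all three visits. The downside is small: the proportional-odds assumption and sparse categories must be checked.
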